## Abstract

**Background:**

The rising incidence of cancer and increasing numbers of cancer survivors have resulted in the need to find alternative models of care for cancer follow-up care. The acceptability for follow-up care in general practice is growing, and acceptance increases with shared-care models where oncologists continue to oversee the care. However, a major barrier to this model is the effective exchange of information in real time between oncologists and general practitioners. Improved communication technology plays an important role in the acceptability and feasibility of shared cancer follow-up care.

**Objective:**

The aim of this study is to evaluate the feasibility and acceptability of a shared cancer follow-up model of care between patients, general practitioners and radiation oncologists.

**Methods:**

This is a mixed methods, multisite implementation study exploring shared follow-up care for breast, colorectal, and prostate cancer patients treated with curative radiotherapy in New South Wales, Australia. This study uses web-based technology to support general practitioners in performing some aspects of routine radiotherapy follow-up care, while being overseen by a radiation oncologist in real time. The study has two phases: Phase 1 is designed to establish the level of agreement between general practitioners and radiation oncologists and Phase 2 is designed to implement shared follow-up care into practice and to evaluate this implementation.

**Results:**

Recruitment of radiation oncologists, patients, and general practitioners commenced in December 2020 and will continue until February 2021. Data collection will occur during 2021, and data will be ready for analysis by the end of 2021.

**Conclusions:**

Few studies have investigated the role of health technologies in supporting communication deficiencies for shared cancer follow-up care. The implementation and evaluation of models of care need to be conducted using a person-centered approach that is responsive to patients’ preferences and needs. Should the findings of the study be acceptable and feasible to radiation oncologists, general practitioners, and patients, it can be quickly implemented and expanded to other tumor groups or to medical oncology and hematology.

**Trial Registration:**

Australian New Zealand Clinical Trials Registry ACTRN12620001083987; http://www.anzctr.org.au/Trial/Registration/TrialReview.aspx?id=380057

**International Registered Report Identifier (IRRID):**

PRR1-10.2196/21752

## Introduction

The increasing incidence of cancer, coupled with improved survivorship, has resulted in higher demand for cancer follow-up care [1-3]. This has led to the sustainability of oncologist-led cancer follow-up care in the secondary health setting being questioned [4,5] and to a call for alternative models of cancer follow-up care [6,7]. There is a growing body of literature on the benefits of shared cancer follow-up models between general practitioners and oncologists [8]; however, this is yet to be integrated into routine practice.

Randomized controlled trials have shown that cancer follow-up care delivered by a general practitioner in the primary health care setting produces no difference in the rate of recurrence or quality of life compared to cancer follow-up with an oncologist [9-11]. General practitioners are willing to take a greater role in cancer follow-up care [12] provided they are supported by the oncologist [13-16] and the oncologist maintains overall responsibility [17].

Despite an acceptance by patients for their general practitioner to be involved in their follow-up care, barriers to shared care exist. The barriers are role clarification [18-20] and effective two-way communication [21-25]. There is a need for a robust information-sharing system that allows both the general practitioner and the overseeing oncologist to be involved in the follow-up care. Real-time and open access to patient information is crucial to coordinate the care of cancer survivors appropriately [26-28].

At present, cancer patients maintain follow-up with their oncologists in the secondary health care setting, and routine communication is transferred from the oncologist to the general practitioner via letter or secure email. In the case where a general practitioner has undertaken a cancer-specific follow-up, it is uncommon for the general practitioner to communicate their findings to the oncologist. This study will trial a web-based technology to breach the communication divide between the general practitioner and the oncologist so that they can work together collaboratively, should patients choose a shared-care model.

To our knowledge, there is currently no system that supports the involvement of general practitioners in shared cancer follow-up care where the radiation oncologist can oversee the care. This study trials a web-based system that allows general practitioners to undertake routine aspects of cancer follow-up care, while sharing the data with oncologists at the hospital in real time so that they can continue to monitor, oversee, and maintain responsibility for the patient.

This research aims to evaluate the feasibility and acceptability of a shared cancer follow-up model of care between patients, general practitioners and radiation oncologists. The objectives of this study are to implement a model of care using a web-based system that transfers clinical information between the general practitioner and radiation oncologist in real time, to determine the level of agreement between general practitioners and oncologists completing a standardized follow-up assessment, and to establish the feasibility and acceptability of this model of care.

## Methods

### Study Design

This research is a mixed methods, multisite implementation study for breast, colorectal, and prostate cancer patients who have undertaken curative radiotherapy treatment. Mixed methods investigations involve integrating quantitative and qualitative data collection and analysis into a single study [29] and can strengthen the credibility of evidence and evaluation [30].

The study will implement the shared cancer follow-up model of care into practice at baseline (Phase 1) and at 6 months postrecruitment (Phase 2) (see Figure 1). During Phase 1, there will be a standard clinical review by the radiation oncologist as per the patient's routine follow-up schedule, plus an additional follow-up review by the general practitioner using the same standardized follow-up assessment. This first phase will determine the level of agreement between general practitioners and radiation oncologists when completing the same radiotherapy follow-up clinical assessment on the patient. This first phase is essential, as it informs the educational and training requirements for general practitioners. By demonstrating the level of agreement, it reassures both the general practitioner and radiation oncologist that the general practitioner can reliably conduct a cancer-specific follow-up review.

**Figure 1 figure1:**
[figure not shown]
Flow diagram of study phases. GP: general practitioner.

The second phase of the study is the implementation of the shared cancer follow-up model of care into practice. The patient will visit their general practitioner at 3.5 years follow-up for a radiation oncology–specific follow-up appointment. The results will be transferred to the hospital, and the patient's radiation oncologist will be alerted by an automatic quality checklist to review the outcomes of the review in real time on the hospital's oncology information system. The system has a rapid referral built into it in the case of adverse events or should the general practitioner suspect cancer recurrence.

### Study Setting

The research will be conducted within the Illawarra Shoalhaven Local Health District (ISLHD) region in New South Wales, Australia. The ISLHD provides public health services to over 400,000 people and cancer services to almost 9000 people annually (ie, medical oncology, hematology, and radiation oncology). Radiation oncology outpatient services are provided at Wollongong Hospital (ie, tertiary hospital and regional care) and the Shoalhaven District Memorial Hospital (ie, secondary hospital and rural care).

The ISLHD radiation oncology service consults and treats over 1400 patients with radiotherapy and conducts over 5000 follow-up consultations annually. The service has experienced a 20% increase in follow-up consultations over a 5-year period (2015-2019), and treatment activity is projected to increase by 18% by 2031. A substantial proportion of radiotherapy treatment at each site is attributed to breast, colorectal, and prostate cancer.

The study will take place at the two hospital radiation oncology outpatient clinics and in the referring general practices. The relationship between general practice and local health districts in Australia is increasingly pivotal to the health system. General practice in Australia is typically comprised of small businesses with an average of three to five general practitioners, and a universal medical insurance scheme (ie, Medicare) covers all or part of a person’s cost to visit a general practitioner [31].

### Local Follow-Up Guidelines

While there are many statements regarding “standard follow-up practices,” postradiotherapy follow-up for patients varies greatly depending on the disease type, the oncologist's preference, and the patient's preference. At the ISLHD, a visit 6 weeks after radiotherapy is routine for most cases to review the settling of acute side effects. The pattern of remaining follow-up sessions for all cancers will include a period of every 3 months for the first year and every 6 months for the second year, followed by yearly reviews and then, finally, discharge from follow-up. For many cancers, a 5-year period of follow-up is common.

At the ISLHD, an acceptable practice for breast cancer patients’ postradiotherapy follow-up care would be a follow-up at 6 weeks, then every 3 months for 2 years, then every 6 months to 5 years, and then yearly to 10 years. An acceptable practice for colorectal cancer patients would be follow-ups every 6 months for the first year and then yearly to 5 years. An acceptable practice for prostate cancer patients would be follow-ups every 6 months or yearly to 5 years. However, the actual frequency depends on the individual patient's health, stage, and treatment and their preference for whom to see; in addition, there is currently no early discharge, transfer of care, or shared care for radiation oncology follow-up care to general practitioners.

### Health Technology

The free and open source software framework PROsaiq (Didymo Pty Ltd) will be used [32]. PROsaiq is based around a web server that extracts assessments from inside the oncology information system and encodes the assessment data into XForms (ie, an XML format used for collecting inputs from web forms), which is then presented as a webpage in a web browser. When the clinical assessment is completed on a smart device (ie, phone, computer, or tablet), the clinical assessment is returned to the web server and converted into a Health Level Seven (HL7) message; HL7 is an accepted international communication standard for clinical systems, such as those comprising laboratory information. The HL7 message is presented to the oncology information system MOSAIQ (Elekta AB), where it is imported to become part of the patient's oncological record.

Australia is equipped with reliable internet capability, and the webpage link will be made available to the general practitioner by integrating it into a current local system that they utilize. The general practitioner will complete the patient follow-up clinical assessments using PROsaiq, and the radiation oncologist will receive an automated alert in real time to review the results at the hospital. PROsaiq has been trialed for the collection of cancer patient–reported quality-of-life outcomes from patients and has demonstrated its operational feasibility [33].

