### Implementation

The foundation of this shared cancer follow-up model of care is that clinician communication exchange is two-way and in real time, while the radiation oncologist continues to oversee the follow-up care. The model includes real-time transfer of results, internal system alerts, and rapid referral to address any issues that may arise. During this study, patients maintain their current specialist standard follow-up care, with all relevant specialists, and will continue follow-up care with their radiation oncologist upon completion of the study.

General practitioners will complete a standardized online radiation oncology course developed by the Cancer Institute New South Wales [36]. The course developed for health professionals addresses the principles of radiation therapy, patient assessment grading systems of side effects, and supportive care management. General practitioners will receive one-on-one training by a radiation oncologist that includes localized radiotherapy-specific follow-up care, a review of the recruited patient’s treatment background, and a demonstration of the clinical follow-up assessment that the general practitioner will use in the patient's follow-up review.

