#### Quantitative Data

The quantitative data will be collected from Phase 1. The radiation oncologist will enter the clinical assessment directly into the oncology information system, while the general practitioners will enter the clinical assessment on the webpage link that will be provided to the general practitioner. Both sets of data from these clinical assessments will be stored in the hospital oncology information system.

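### Where the general practitioner reviews first in Phase 1, the radiation oncologist can see those grades before rating, so measured agreement may be inflated

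*Protocol article*

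**What the plan says.** All references are to the protocol article.

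- **Purpose of Phase 1 (Study Design).** "This first phase will determine the level of agreement between general practitioners and radiation oncologists when completing the same radiotherapy follow-up clinical assessment". The same paragraph says that the result is to reassure both clinicians that the GP can do this review reliably.
- **The two reviews (Study Design).** The RO carries out the routine review, "plus an additional follow-up review by the general practitioner using the same standardized follow-up assessment". The article gives no order, no interval and no masking.
- **The model runs in both phases (Study Design).** "The study will implement the shared cancer follow-up model of care into practice at baseline (Phase 1) and at 6 months postrecruitment (Phase 2"). Under Implementation, real-time transfer of results and system alerts are listed as parts of that model.
- **Path of the GP's form (Health Technology).** The form is sent to the hospital oncology information system, "where it is imported to become part of the patient's oncological record", and "the radiation oncologist will receive an automated alert in real time to review the results at the hospital". Neither step is restricted to a phase.
- **Path of the RO's form (Data Collection, Quantitative Data).** In Phase 1 the RO enters grades directly into the oncology information system. "Both sets of data from these clinical assessments will be stored in the hospital oncology information system".
- **Analysis (Data Analyses, Quantitative Data).** Cohen's kappa and percent agreement are computed for each item, and a value above 0.81 is expected on every item. Results go back to the clinicians to steer further training.
- **Limitations.** The number of participants and the raters' different viewpoints are named. Loss of independence between the ratings is not.

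**The concern.** Kappa can be read as inter-rater reliability only if each rater grades without knowing the other's grades. The information flow that makes the shared-care model work in practice runs against this. It delivers the first rater's grades, with a prompt to read them, into the system where the second rater will enter theirs. An RO who has just read a GP's grade of 1 for fatigue is more likely to enter 1.

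Agreement is the only quantitative analysis the article describes. It supports the statement that GPs can do the review reliably, and it decides where more training is needed. Inflated agreement would support the first too readily and hide the second.

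**Working it through.** **Is there a stated path from one rater to the other?** The article gives no figure to reproduce here, so the first step is to set the sections side by side.

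1. The model, which includes transfer and alerts, is implemented at baseline as Phase 1 (Study Design, Implementation).
2. The GP's completed form enters the patient's record and triggers an alert to the RO, with no phase limit (Health Technology).
3. The RO enters Phase 1 grades into the same system (Data Collection).
4. No section fixes the order of the reviews or withholds the first set of grades.

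If the GP reviews first, following the plan as written prompts the RO to read the GP's grades before rating. If the RO reviews first, this path cannot affect the RO's grades.

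**How large could the effect be?** The article gives neither the true agreement nor the share of copied ratings, so both are assumed and shown over a range. Let f be the share of second ratings copied from the first, po the true agreement and pe the chance agreement. With equal rater marginals, copying leaves pe unchanged:

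- observed agreement = f + (1 − f) × po
- expected kappa = [f + (1 − f) × po − pe] / (1 − pe) = f + (1 − f) × true kappa

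For a true kappa of 0.6:

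- f = 10%: 0.10 + 0.90 × 0.6 = 0.64
- f = 25%: 0.25 + 0.75 × 0.6 = 0.70
- f = 50%: 0.50 + 0.50 × 0.6 = 0.80

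The formula was checked by simulation with 20 pairs (the planned number of triads), a 0 to 4 scale, assumed marginals 0.50, 0.25, 0.15, 0.07 and 0.03, and 10,000 runs per setting. Each cell gives expected kappa from the formula, then the simulated chance that one item's kappa exceeds 0.81.

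| True kappa | f = 0 | f = 10% | f = 25% | f = 50% |
|---|---|---|---|---|
| 0.5 | 0.50; 1.7% | 0.55; 3.4% | 0.625; 8.5% | 0.75; 32.2% |
| 0.6 | 0.60; 6.4% | 0.64; 10.5% | 0.70; 19.8% | 0.80; 48.2% |
| 0.7 | 0.70; 19.7% | 0.73; 26.2% | 0.775; 39.0% | 0.85; 65.9% |

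Simulated mean kappas lie slightly below the formula, as expected in small samples (for example 0.688 against 0.70 for true kappa 0.6 and f = 25%).

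**Copying needed for an expected kappa of 0.81:** f = (0.81 − true kappa) / (1 − true kappa).

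- True kappa 0.5: 0.31 / 0.5 = 62%, about 12 of 20 pairs
- True kappa 0.6: 0.21 / 0.4 = 52.5%, 10 to 11 of 20
- True kappa 0.7: 0.11 / 0.3 = 37%, about 7 of 20
- True kappa 0.8: 0.01 / 0.2 = 5%, 1 of 20

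Twenty pairs is the most any item can have. Items that Table 1 lists for only one tumor type will have fewer if all three types are enrolled, and each copied rating then weighs more.

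**The case against.** **The alert belongs to Phase 2.** The alert workflow is spelled out in the paragraph on the second phase, and Health Technology is a general description. This has some force. But that description has no phase limit, the model with its alerts is said to be implemented at baseline, and both Phase 1 forms sit in one system. Even without an alert, the GP's grades would be in the record the RO is using.

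**A condensed article may leave masking and visit order to the full protocol.** That is fair, and silence alone would not carry the point. It rests instead on stated flows that work against independence. If the full protocol masks the raters, one sentence in the article settles the matter.

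**Little depends on the result.** The 0.81 value is an expectation and not a stated condition for entering Phase 2. The study concerns feasibility and acceptability, and patients keep their specialist follow-up. This stands and limits the consequence to the reading of kappa and the choice of training.

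**Stronger readings that the article does not support:**

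- *The training contaminates the ratings.* A reader might infer this from "General practitioners will receive one-on-one training by a radiation oncologist", which covers the recruited patient. But the trainer is not said to be that patient's own RO, and the content is treatment background and a demonstration of the form, not current grades. Training raters on a scale can legitimately raise true agreement.
- *The RO's letter contaminates the GP's rating.* The Introduction says that "routine communication is transferred from the oncologist to the general practitioner via letter or secure email". That is background on present practice. Nothing says the letter carries item grades or arrives before the GP's Phase 1 review.
- *Agreement will certainly be inflated.* The order is unstated, shared storage does not show that anyone reads the other form before rating, and a gap between reviews can lower agreement on symptoms that change. The net direction in the trial is not known.

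**Conclusion.** The point holds as a risk of bias, limited to the path from GP to RO and to pairs in which the GP reviews first. In those pairs the plan as written lets the RO see the GP's grades, and prompts the RO to look at them, before rating. Kappa and percent agreement may then partly reflect information flow and not the GP's own grading.

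The size cannot be known from the article. Under the assumptions of equal marginals and a copied share of 10% to 50%, a true kappa of 0.6 would be expected to appear as 0.64 to 0.80, and 0.7 as 0.73 to 0.85. Modest copying does not carry a poor item past 0.81, but it can make a moderate item look good enough that a training need is missed. Analysis cannot recover independent ratings once the forms are complete, so the matter should be settled before the Phase 1 reviews.

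**What to change.** For the Phase 1 agreement ratings only:

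- Each rater submits and locks their own form before opening the other's item grades. Safety alerts, rapid referral and clinical oversight stay unchanged. If an RO opens the GP's form earlier for a clinical reason, the pair is recorded as unmasked.
- Record the date of each review and, with one tick-box, whether the form was completed without sight of the other.
- Keep all pairs. Report kappa and percent agreement with and without the unmasked pairs, and by the interval between reviews. With at most 20 pairs per item, excluding pairs outright by a fixed window would cost too much information.

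If masking is not possible, add non-independence of the ratings to Limitations and do not present kappa as independent inter-rater reliability.

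The cost is a sentence or two of protocol wording, a tick-box and a recorded date on each form, and slightly more coordination. The researcher already helps to arrange appointments. The estimate without unmasked pairs will be less precise, which is why both are shown.

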### Eligibility Criteria

To be eligible for the study, patients must (1) have a previous diagnosis of colorectal, breast, or prostate cancer; (2) have completed curative-intent radiotherapy treatment and are due for their 3-year review; (3) be over 18 years of age; (4) be able to understand and speak English; and (5) have a general practitioner willing to participate. Patients who do not meet these criteria will be excluded, as will patients who have suspected or confirmed recurrence of cancer.

Patients 3 years posttreatment have been selected, as it was deemed a safe time period by the oncologists for a feasibility study, and the patients will have experienced the standard oncologist-led follow-up model. Participants can withdraw at any stage up until data analysis.

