### Sample Size

The sample will consist of 20 triads comprising the patient, their radiation oncologist, and their general practitioner, for a total of 35 to 45 participants. A total of 10 patients will be from the Wollongong Cancer Centre (ie, regional) and 10 will be from the Shoalhaven Cancer Centre (ie, rural).

Sample size guidelines for qualitative interviews suggest that a range between 20 and 30 interviews is adequate for each group to reach data saturation [34]. The sample size for the quantitative level of agreement data requires a minimum of 5 samples; however, to increase the confidence interval, a higher sample is required [35].

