### Recruitment

The radiation oncologists will review their follow-up clinic lists from both sites and screen for initial inclusion criteria. The researcher will invite each patient to participate via a postal letter on behalf of the radiation oncologist. Once each patient consents to participate, their general practitioner will be invited. General practitioners will be eligible for continuing professional development points for participating. If the general practitioners do not consent to participate, the patient will not be eligible.

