### Data Collection

#### Overview

The PROsaiq software will be used to administer clinical assessments. The assessments were compiled internally at the ISLHD for follow-up of radiotherapy patients. These clinical assessments review physical items on a scale from 0 to 4 for items specific to radiotherapy follow-up care, such as pain, fatigue, physical performance, bowel issues, urinary issues, and appetite (see Table 1). The included scales were sourced from the Radiation Therapy Oncology Group scales [37] and the Common Terminology Criteria for Adverse Events, version 3.0 [38].

**Table 1 table1:** Radiation oncology follow-up standardized clinical assessment.

Tumor type	Clinical assessments
Breast	Fatigue, ECOG (Eastern Cooperative Oncology Group) Performance Status, appetite, weight loss, chest and breast pain, telangiectasia, lymphedema-related fibrosis, and disease state (ie, local, regional, or distant)
Colorectal	Fatigue, ECOG Performance Status, appetite, weight loss, proctitis, pelvic pain, vomiting, and diarrhea
Prostate	Fatigue, ECOG Performance Status, erectile dysfunction, dysuria, and rectal hemorrhage

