### Data Analyses

#### Quantitative Data

The clinical assessment data will be extracted from the oncology information system; the Cohen κ value and percent agreement for each variable from Table 1 will determine the level of agreement between general practitioners and radiation oncologists. The agreement will assess the concordance between two measurements of each variable with the expectation that there will be near-perfect agreement on each item (>0.81). The results of the analysis and level of agreement will be presented to the general practitioners and radiation oncologists to guide any additional education and training.

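### Because recurrence is excluded at entry, agreement on the breast disease-state item cannot be judged against >0.81 and says almost nothing about whether GPs recognise recurrence

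*Protocol article*

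**What the plan says.** All references are to the protocol article.

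- **Eligibility Criteria.** Patients "have completed curative-intent radiotherapy treatment and are due for their 3-year review". Those who fail the criteria are excluded, "as will patients who have suspected or confirmed recurrence of cancer".
- **Recruitment.** "The radiation oncologists will review their follow-up clinic lists from both sites and screen for initial inclusion criteria". The oncologists who screen are therefore also the clinicians whose ratings are compared with the GP's.
- **Data Collection, Overview, Table 1.** The breast assessment ends with "disease state (ie, local, regional, or distant". The colorectal and prostate assessments have no such item.
- **Data Analyses, Quantitative Data.** "the Cohen κ value and percent agreement for each variable from Table 1 will determine the level of agreement", "with the expectation that there will be near-perfect agreement on each item (>0.81". No item is treated separately. The results go back to both groups of clinicians to guide training.
- **Sample Size.** "The sample will consist of 20 triads comprising the patient, their radiation oncologist, and their general practitioner". The split by tumour type is not given.
- **Study Design.** Showing the level of agreement in Phase 1 is said to reassure both clinicians that "the general practitioner can reliably conduct a cancer-specific follow-up review". The Phase 2 description below Figure 1 names two triggers for rapid referral: adverse events, and GP suspicion of recurrence.

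**The concern.** Agreement statistics are informative only when the rated trait varies. The entry exclusion removes nearly all variation in disease state, yet the analysis section holds this item to the same measures and expectation as the toxicity and performance items.

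Two things follow. First, κ cannot do its job here, so the stated expectation has no usable answer for this item. Second, percent agreement may be high in a group with no recurrence to find. A colleague reading it beside the other items, under a general statement about cancer-specific review, could take it as evidence that GPs notice recurrence. Phase 2 relies on that skill for one of its referral triggers, and the same results decide whether more GP training is offered.

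**Working it through.** **Plan's own figures.** The plan gives 20 triads, a cited minimum of 5 samples for agreement, and an expected level above 0.81. It gives no null value, power or precision target, so the sample size cannot be re-derived. The check asks instead what the planned statistics can show for this item.

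**Assumptions (not in the article).** The probability p that a screened-clear patient has a recurrence at the Phase 1 visit is 0% to 5%. The number of breast patients n is 5 to 20, or about 7 if the three tumour types are equally represented (20/3 ≈ 6.7). The oncologist's rating is taken as the reference, and the item is reduced to recurrence recorded or not.

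**Step 1: κ when the oncologist records no recurrence in anyone.** Let the GP flag f of n patients. Observed agreement is po = (n − f)/n. The oncologist's ratings are constant, so chance agreement is also pe = (n − f)/n. With κ = (po − pe)/(1 − pe):
- f = 0: po = pe = 1, so κ = 0/0 (undefined), with agreement 100%.
- f = 1: κ = 0, with agreement 6/7 = 86%, 9/10 = 90% or 19/20 = 95%.
- The reverse case, one recurrence recorded by the oncologist and missed by the GP, also gives κ = 0 with the same agreement.
- If both flag the same single patient, κ = 1, but that value rests on one patient.

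**Step 2: how often there is a case to detect.** P(no case) = (1 − p)^n, and P(2 or more cases) is the binomial tail.

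| n | No case, p = 1% | No case, p = 2% | No case, p = 5% | 2+ cases, p = 1% | 2+ cases, p = 2% | 2+ cases, p = 5% |
|---|---|---|---|---|---|---|
| 5 | 95% | 90% | 77% | 0.1% | 0.4% | 2.3% |
| 7 | 93% | 87% | 70% | 0.2% | 0.8% | 4.4% |
| 10 | 90% | 82% | 60% | 0.4% | 1.6% | 8.6% |
| 20 | 82% | 67% | 36% | 1.7% | 6.0% | 26.4% |

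The last row is an extreme in which every patient has breast cancer.

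**Step 3: what percent agreement can distinguish.** Expected agreement is p × sensitivity + (1 − p) × specificity. For a GP who never records recurrence (sensitivity 0, specificity 1) this is 1 − p, which is 100%, 99%, 98% and 95% at p = 0%, 1%, 2% and 5%. A GP who detects every case and raises no false alarm has 100%. At p = 5% and n = 7, the two differ by an expected 7 × 0.05 = 0.35 discordant patients.

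**Step 4: sensitivity.** With no case it cannot be estimated. With one case correctly called, the exact two-sided 95% lower bound is 2.5%.

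**The case against.** The strongest reply is that the protocol never says Phase 1 tests recognition of recurrence. It says Phase 1 measures agreement on a shared assessment and informs training, and a cancer-specific review can be read as completing that form. This stands as a limit on the point: the fault is the breadth of one inference, not a false claim about detection. The inference is nevertheless unqualified, and disease state is on the form.

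A reader might infer four stronger things that the documents do not support.

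- **That near-complete agreement is guaranteed whatever the GP's ability.** The exclusion fixes the likely true state, not what the GP records. With assumed GP specificity of 0.90 or 0.95 and no recurrences, the chance that all 7 pairs agree is 0.90^7 = 48% or 0.95^7 = 70%. The item does test over-calling. A new recurrence could also surface after screening.
- **That the item would wrongly pass the benchmark.** In the likeliest outcomes κ is undefined or 0, so it fails to meet 0.81. Misplaced reassurance could come only from percent agreement read alone.
- **That Table 1 lacks a level for patients without disease.** The working form is not shown, and the parenthesis may name sites that are each marked present or absent.
- **That the exclusion is a mistake.** It is a reasonable entry rule for a feasibility study.

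It is also fair to say that this is 1 of 21 item entries in Table 1 (8 + 8 + 5), that other items may vary little too, that oncologists keep oversight, and that patients keep their standard specialist follow-up (Implementation). These facts limit the consequences. They do not make the item informative, and the Limitations section, which cites participant numbers and differing viewpoints, does not cover a trait removed by the entry criteria.

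**Conclusion.** The point holds in a limited form. For the breast disease-state item, the planned κ will most likely be undefined or 0, so the expectation above 0.81 cannot be assessed. Percent agreement can expose false alarms, but it separates a GP who never records recurrence from a perfect one by at most 5 percentage points in expectation over the assumed range. Phase 1 therefore cannot support the recurrence part of the Study Design inference.

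The conclusion rests on the assumed recurrence rate and number of breast patients, since the article gives neither. It weakens only at the extreme of 20 breast patients and a 5% rate. There the chance of no case falls to 36%, but two or more cases are still expected only 26% of the time, too few to estimate sensitivity usefully. This matters for what Phase 1 may claim. It does not undermine the agreement analysis of the other items.

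**What to change.** 1. **Data Analyses, Quantitative Data:** take disease state out of the items judged against the 0.81 level. Report it as the number of breast patients in whom the GP only, the oncologist only, both or neither suspected recurrence.
2. **Study Design:** limit the Phase 1 conclusion to agreement on grading treatment effects and performance status. State that sensitivity to recurrence is not tested, because patients with suspected or confirmed recurrence are excluded at entry.

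The entry criteria, sample size and data collection stay as they are. The cost is a few sentences of wording and a narrower claim for Phase 1.
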